#### Potential Confounding Variables

Previous studies have shown that there are numerous confounding variables that affect patients’ ability to participate in SDM [
15,
17,
18,
59]. In order to account for these variables, demographic information was collected at enrollment (T0). Demographics included age, sex, race/ethnicity, educational attainment, and income level. Clinical characteristics included the number of years diagnosed with diabetes and current diabetes treatment (eg, lifestyle modifications, oral medications, insulin, or both oral medication and insulin).

In the study population, health literacy is also expected to be a significant confounding variable. Health literacy was measured at enrollment (T0) using the Newest Vital Sign (NVS) [
51-
53]. The NVS is a food label accompanied by 6 questions that are scored dichotomously (correct/incorrect). It has been validated against a longer health literacy questionnaire with an area under the receiver operating characteristic curve of .88. A score of less than 2 has a sensitivity of 72% and a specificity of 87% for predicting low health literacy, while a score of less than 4 has a sensitivity and specificity of 100% and 64%, respectively. The NVS also has good internal consistency reliability, with Cronbach’s alpha = .76.

#### Acceptability and Feasibility of the Intervention

Acceptability and feasibility were judged based on (1) willingness of potential research subjects to enroll in the study, (2) responses to the activities during the PEP sessions, and (3) ability to engage in the role-playing scenarios in PEP session 2. After completion of the PEP intervention, all participants were invited to attend a focus group to discuss their experiences with and reactions to the PEP intervention, which were then audiotaped and transcribed. The transcribed text will be parsed into segments that represent a perspective or theme and each segment will then be independently coded by three readers. Through an iterative process among the coders, a single parsimonious coding scheme will be derived and then applied to all transcripts by the same three coders toward providing a thematic analysis of the data.

### Intervention: Patient Empowerment Program

Our PEP is a two-session course led by a clinical health psychologist (LA) and assisted by research staff (JP, SK, and CS). Each session is 2 hours in length and the two sessions are held approximately 1 week apart. The PEP intervention is designed to be a group experience, with 2-6 participants attending each session. Ideally, the same participants who attended session 1 will return for session 2, but because of the limited availability of both research staff as well as participants, it is expected that this may not always be the case.

#### PEP Intervention Development

The PEP intervention curriculum (see
Table 2) and materials for each PEP session were developed with input from patients as well as HCPs across all levels of training. Input was obtained via focus groups, all led by a clinical health psychologist (LA). Six focus groups for patients with T2DM (n=26) were held across all three study sites. In these groups, patients discussed their experiences with HCPs, difficulties managing diabetes, and opinions about participating in the PEP. This information was used to create content for video clips of patient-HCP interactions and cases for role-playing scenarios with SHPs. Overwhelmingly, patients reported that they thought it would be beneficial to participate in a program like PEP [
60].

Focus groups were also held with internal medicine attending physicians (n=11), primary care residents (n=16), and medical students with at least 1 year experience on clinical rotations (n=11). In these groups, HCPs discussed their experiences with patients and expectations for patient engagement/activation. Overwhelmingly, HCPs reported preferring patients who were more informed about their medical conditions, who raised questions or concerns during the office visits, and who performed self-management behaviors in between appointments to those who were less activated [
61].

After these focus groups were completed and intervention materials were created, 6 patients from the focus groups were invited to complete a beta test of the PEP intervention. During the beta test, they provided feedback about timing of the sessions, realism of the video clips, and feasibility of asking patients to complete a 10-minute role-play scenario with SHPs. Their feedback was used to revise all materials before recruitment for the PEP intervention began.

**Table 2 table2:** Patient Empowerment Program intervention curriculum.

	Session 1		Session 2	
Session Element	Part 1	Part 2	Part 1	Part 2
Time	1 hour	1 hour	1 hour	1 hour
Task	Learn disease-specific case & HCP ^a^checklist	Use checklist to rate video interactions	Practice case with SHPs ^a^	Plan to apply model to own health care
Goal	Set standards for high-quality HCP and activated patient behaviors	Understand range of provider behaviors Learn to accurately describe provider behavior	Experience models of physician-patient interactions Shift social dynamic by empowering patient	Increase patient activation
Target	Learn standards for HCP behaviors: listen, ask questions, develop shared goals Learn standards for patient behaviors: share information, make choices, negotiate with provider	Learn to recognize elements of good/poor shared decision making and communication Practice describing HCP and patient behavior	Learn to be an active partner in health care encounters Give constructive feedback to providers	Reflect on lessons learned Set individualized goals for own health care and interaction with HCP
Theory	Develop cognitive framework for health care interactions	Vicarious learning of interpersonal skills in exam room	Behavioral rehearsal Experiential learning	Behavioral intentions

^a^HCP: health care provider; SHP: standardized healthcare provider

#### Intervention Standardization and Fidelity

In order to standardize the intervention, a curriculum and detailed manual were created. A group of 7 actors with previous SP experience were trained to play SHPs at the beginning of the study and reoriented to each case by an SP trainer before each intervention session. Throughout the intervention sessions, participants were asked to rate each activity to determine if the learning goals were being achieved, using a simple visual Likert scale with responses ranging from 0 = not at all to 3 = very much. All PEP intervention sessions were also audiotaped so that they could be transcribed to evaluate consistency across each run of the intervention.

#### Patient Empowerment Program Session 1

In the beginning of PEP session 1, participants discussed their experiences with HCPs and beliefs about the role of the patient and HCP in the medical encounter. Two posters were used to frame this discussion (see
Figure 2), which describe specific behaviors of an effective patient-HCP team (ie, Team Works Well) and one that is not effective (ie, Team Needs Work). This framework was used to anchor discussions of the video clips and role-playing scenarios throughout the remainder of the PEP intervention.

Participants then watched three pairs of video clips of patient-HCP interactions. These video clips were created using actors who were experienced SPs and to represent a range of sex, race, and ethnicity for both the patient and HCP. Each pair of video clips represented a different aspect of a conversation between a patient and HCP, including (1) HCP taking the patient's medical history, (2) HCP providing information, and (3) decision making about the treatment plan. All visits were designed as follow-up visits, implying an ongoing relationship between patient and HCP within the interactions.

The first video in each pair represented a negative example of communication. In these videos, the patients were passive and did not voice their perspective or engage actively with the HCP. The HCPs, while trying to be helpful and sympathetic, were rushed, followed their own agendas, and acted with some sense that they knew the best approach. After the video clip, participants rated both the patient’s and HCP’s communication based on behaviors listed on the Team Works Well poster and discussed what each party could have done to improve the communication and the quality of the visit.

The second video in each pair was example of positive communication in the same situation. The patients in these videos were more activated and engaged with their HCPs, while the HCPs demonstrated a patient-centered approach. Similar to the first video, afterwards participants rated the patient and HCP and then had a brief discussion about what was different or improved.

**Figure 2 figure2:**
[figure not shown]
Framework for patientÃƒÆ’Ã†â€™Ãƒâ€šÃ‚Â¢ÃƒÆ’Ã‚Â¢ÃƒÂ¢Ã¢â€šÂ¬Ã…Â¡Ãƒâ€šÃ‚Â¬ÃƒÆ’Ã‚Â¢ÃƒÂ¢Ã¢â‚¬Å¡Ã‚Â¬Ãƒâ€¦Ã¢â‚¬Å“health care provider interactions.

#### Patient Empowerment Program Session 2

PEP session 2 gave participants the opportunity to practice the communication skills that were discussed in session 1. Participants were first split into pairs to complete a brief role-play scenario with SHPs. While one participant was role-playing, the other observed and rated both the participant and the SHP in real time. The observing participant then led a debriefing of the scenario in order to practice giving feedback. After the debriefing, the participants switched places and the second participant completed a different role-play scenario.

In the second part of PEP session 2, participants applied what they learned to an individualized 10-minute role-play scenario with a SHP, created specifically for each participant based on self-reported difficulties with diabetes. Common topics for this scenario included struggles with adhering to a healthy diet, difficulties performing frequent finger sticks to monitor blood glucose, and overall frustration when trying to control blood sugar numbers. Research personnel observed these role-plays and led a debriefing afterward. PEP session 2 concluded with a group discussion about lessons learned from the role-plays and each participant worked with a member of the research staff to create an individualized action plan for both diabetes self-care and future medical encounters. All ideas for the action plan were participant generated, but research staff provided feedback on the feasibility of their goals and brought up potential barriers to those goals when participants were unable to identify any on their own.

#### Post-PEP Focus Group

Approximately 1 week after the completion of PEP session 2 all participants were invited to attend a focus group. The goals of focus group were to (1) collect the first set of follow-up questionnaires, (2) gather qualitative data on intervention, and (3) get feedback on each element of the PEP curriculum.

### Follow-Up

After completion of the PEP intervention, participants will be followed up for 6 months and will complete repeat assessments at 1 week (T2), 3 months (T3), and 6 months (T4) after the PEP intervention (see
Table 1). The T2 assessment will take place either at the beginning of the focus group, to avoid any bias introduced by discussing the PEP intervention again, or by telephone for any participants who do not come to the focus group. The T3 and T4 follow-ups will occur by telephone and any concurrent HbA
_1c_available at these times will be collected from the EMR.

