### Recruitment, Randomization, and Retention

Research assistants (RAs) screened all of the clinic appointments each day to identify patients who were eligible for the study. Research assistants then briefly explained the study to all eligible patients who came to their appointment and obtained informed consent from those who decided to enroll (see
Figure 1). After obtaining informed consent, RAs read participants a set of questionnaires to complete the initial (T0) assessment (see
Table 1).

After 20 participants were enrolled in the study, a Web-based random number generator was used to generate a list of 20 integers between one and two. The list was refreshed until it contained 10 ones and 10 twos. Based on this list, participants were assigned in order of their study identification number to the immediate intervention (1) or deferred intervention (2) group. All participants in the immediate intervention group were contacted by phone to schedule the PEP intervention sessions and all participants in the deferred intervention group were contacted by phone and informed that they would be recontacted in 3-4 months to schedule their PEP intervention sessions.

Participants were compensated for participating in the study. They received US $10 and a MetroCard with US $10 at each of the two PEP intervention sessions. They also received US $60 and a MetroCard with US $10 for completing the study if they attended a post-PEP focus group.

In order to increase retention of deferred intervention participants, they received a letter from our program and an educational handout about T2DM in the mail approximately every 3 weeks. Handouts were sent in the same order and all handouts came from the Diabetes Care and Education website [
50]. In total there were four mailings: (1) Nutrition to Help Manage your Diabetes and Weight, (2) Eating Healthy on a Lean Budget, (3) Know Your Blood Sugar Numbers, and (4) Managing and Preventing Hypoglycemia. All four of these handouts were short, only 1-2 pages in length, and contained general information about T2DM that participants should have already obtained from their HCPs as part of their routine treatment. Therefore, we do not expect that receiving these handouts will cause a significant difference in the two randomized groups or otherwise affect the results of the study.

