#### Primary Outcome

The primary outcome of the study is patient activation, as measured by the short form of the PAM [
23]. The PAM is a 13-item interval level, unidimensional, Guttman-like scale with four response options, ranging from 1 = disagree strongly to 4 = agree strongly. It has been validated across multiple patient populations and has been shown to be reliable, with Rasch person reliability estimates ranging from .73-.84. The overall score on the PAM ranges from 0-100 and PAM scores can be categorized into four levels of activation. In level one, the lowest level, patients believe taking an active role in their health is important but are unprepared for this role. In level two, patients have some knowledge but still struggle to manage their medical conditions. In level three, patients begin to take action in terms of self-management but do not have the skills to support or sustain their behavior. Finally, in level four, patients have adopted self-management behaviors and work on maintaining them in stressful life situations [
23,
30].

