### Data Analysis

First, descriptive statistics including mean, standard deviation, range, skewness, and kurtosis for all continuous variables as well as frequencies for all categorical variables will be calculated at each time point (T0-T4). Because of concerns about the relatively small sample size and low literacy/health literacy, the normality of all continuous variables will be assessed both graphically with histograms as well as statistically using the Shapiro-Wilk and Kolmogorov-Smirnov tests, and transformations will be made if necessary. Then we will assess for any baseline (T0) differences between two separate groups: (1) the randomly determined immediate intervention and deferred intervention groups and (2) all participants who attended the PEP intervention and those who did not. Both of these analyses will be conducted using chi-square test for categorical variables and either independent samples
*t*test or Wilcoxon rank sum test for continuous variables.

Next, analyses will be conducted within each intervention group to evaluate for any effect of the PEP intervention on the primary, secondary, and exploratory outcomes using chi-square test for categorical variables (eg, PAM level, PCS) and either repeated-measures
*t*test or Wilcoxon signed rank test for continuous variables (eg, PAM score, AURA, Krantz, SF-12v2 Health Survey, DSMQ, and HbA
_1c_). Initial assessment (T0) will be compared with each of the post-PEP assessments (T2-T4) for each variable. For the deferred intervention group, initial assessment (T0) will be compared with the assessment at the end of the waiting period (T1), which will then be compared with each post-PEP assessment (T2-T4).

After analyzing each group individually, the groups will be combined in order to have a larger sample size for pre- and post-PEP comparisons. Pre-PEP intervention data for these analyses will consist of data from enrollment (T0) for participants in the immediate intervention group and data collected at the end of the waiting period (T1) for participants in the deferred intervention group. Repeated-measures analyses will be conducted on the primary, secondary, and exploratory outcomes as described above and pre-PEP data (either T0 or T1) will be compared with each post-PEP assessment (T2-T3).

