Finally, multivariate analyses will be conducted using a series of generalized mixed-effects models to determine what effect patient characteristics, group membership, and time have on each continuous outcome measure. In each model, the dependent variable will be the outcome measure (eg, PAM, AURA, Krantz, SF-12v2 Health Survey, DSMQ, and HbA
_1c_). Independent variables will include participant characteristics such as age, sex, race/ethnicity, education level, annual income, number of years with T2DM, and health literacy as measured by the NVS. Other independent variables will include group (immediate vs deferred intervention) and time (T0-T4).

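### In the immediate arm, and in its share of the pooled pre-post analysis, an in-person baseline is compared with telephone T3 and T4, so an interview-mode shift would be counted as a PEP effect

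*Protocol article*

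**What the plan says.** **Outcome.** "The primary outcome of the study is patient activation, as measured by the short form of the PAM". The secondary questionnaires (AURA, Krantz, Preference Control Scale, SF-12v2, DSMQ) are also answers given to a research assistant (RA), who reads the items aloud. Outcome Measures describes a standardized way of asking and clarifying questions. It does not mention the channel.

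**Mode at each time point.**
- T0: RAs "briefly explained the study to all eligible patients who came to their appointment", and then "After obtaining informed consent, RAs read participants a set of questionnaires to complete the initial (T0) assessment". In person is the natural reading, but it is not stated.
- T1 (deferred arm, end of waiting period): mode not stated. Sample Size says only that participants were contacted for it.
- T2: at the start of the focus group, "or by telephone for any participants who do not come to the focus group".
- T3 and T4: "The T3 and T4 follow-ups will occur by telephone".

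**Analyses.** Data Analysis specifies paired tests within each group: "Initial assessment (T0) will be compared with each of the post-PEP assessments (T2-T4) for each variable". In the deferred arm, T0 is also compared with T1, and T1 with T2 to T4. A pooled analysis then takes T0 (immediate) or T1 (deferred) as the pre value; as written, its post values are T2 and T3. The mixed models use patient characteristics, and "Other independent variables will include group (immediate vs deferred intervention) and time (T0-T4"). Interview mode is not among the listed terms.

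**The concern.** A paired change from T0 to T3 or T4 is to be read as the effect of PEP. In the immediate arm that change spans two things at once: receiving PEP, and moving from a clinic interview to a telephone interview. No pair in that arm has one without the other at T3 or T4, so the paired test cannot tell them apart. In the mixed model the time label carries the same switch.

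Every questionnaire outcome is spoken to study staff, so a modest difference in how people answer in clinic and by telephone is plausible. It could be reported as improved activation or self-management, or it could hide a real gain. The article itself accepts that circumstances of administration matter, since it places T2 before the focus group discussion to avoid bias. HbA1c comes from the medical record and is not affected.

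**Working it through.** **1. Which comparison is the study sized on?** Inputs from Sample Size: d = 0.48, alpha = .05, beta = .2, n = 36.
- Paired test, two-sided, normal approximation: (1.960 + 0.842)² / 0.48² = 34.07, so 35.
- Paired test, two-sided, noncentral t: 37, with power 79.96% at n = 36.
- One-sided normal: 26.8, so 27. Two-sample: 2 × 34.07 = 68.1, so 69 per arm.

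The stated 36 is thus a two-sided pre-post figure, the kind of comparison that a mode shift can distort.

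**2. Mode of each planned comparison.**

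| Comparison | Mode |
|---|---|
| Immediate T0 vs T2 | mostly same (in person); no DSMQ or SF-12v2 at T2 (Table 1) |
| Immediate T0 vs T3, T4 | crosses modes in every pair |
| Deferred T0 vs T1 (no PEP between) | crosses modes if T1 by telephone, same if in person |
| Deferred T1 vs T3, T4 | same if T1 by telephone, crosses if in person |
| Pooled pre vs T3 | immediate pairs cross; deferred pairs depend on T1 |

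Attendance so far (Results): 33 returned for the focus group, which is 33/36 = 92% of full completers or 33/45 = 73% of session 1 attenders.

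**3. Sensitivity to an assumed shift.** The documents give no mode effect, so the shift δ (in SD of the score) is assumed. There is no PEP effect. With pre-post correlation ρ, the SD of a paired difference is √(2(1−ρ)), which is 1 at ρ = 0.5. The rejection rate is the two-sided noncentral t probability with noncentrality √n × mean shift / SD of difference.

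| ρ = 0.5 | δ = 0.1 | δ = 0.2 | δ = 0.3 |
|---|---|---|---|
| n = 36, all pre values in person | 9.0% | 21.5% | 41.7% |
| n = 36, T1 by telephone, 18 of 36 pairs deferred (mean shift δ/2) | 6.0% | 9.0% | 14.1% |
| n = 20, immediate arm alone | 7.1% | 13.6% | 24.7% |

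The second row ignores the added spread from mixing two kinds of pairs; simulation that includes it gives 6.0%, 8.9% and 13.5%. At ρ = 0.7 and δ = 0.2 the three rows become about 33%, 11-12% and 20%.

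**4. In PAM points.** The stated 4 to 8 points at d = 0.48 imply an SD of 4/0.48 = 8.3 to 8/0.48 = 16.7. A shift of 0.2 SD is then 1.7 to 3.3 points. Put the other way, a 2-point shift with no PEP effect gives rejection at n = 36 in 29% of trials at SD 8.3, 15% at SD 12.5 and 11% at SD 16.7.

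**The case against.** A reader might infer that no analysis separates interview mode from PEP. The documents do not support that. T0-T2 is planned for PAM and is mostly in person on both sides. The deferred T0-T1 comparison contains no PEP, so with a telephone T1 it would show mode plus time alone, and T1-T3/T4 would be mode-matched. These points stand, and they confine the problem to the comparisons named here. They do not remove it. The T1 mode is not fixed, so the deferred arm's protection is not secured. T2 is only 1 week after PEP and omits DSMQ and SF-12v2, so self-management has no same-mode comparison in the immediate arm.

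A reader might also infer that the results will be biased. That is not shown either. In both channels an RA reads the items and records the answers, so the contrast is not interview against self-completion. The size and direction of a shift are assumed, and the largest rates above require every T1 to be in person. In-person T0 is itself an inference.

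Mode details could sit in a fuller protocol or SAP. That is fair for T1. But the article fixes telephone for T3/T4 and fixes T0 against T3/T4 as a test of PEP, and the problem lies in that combination.

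Finally, one might base all T3/T4 inference on same-mode pairs, or make in-person T2 the main result. The objections to both stand. At 18 pairs and d = 0.48 the power is about 48%, against 80% at 36, and choosing in-person T2 conditions on coming back to a paid focus group after the intervention.

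**Conclusion.** The point holds for T0 against T3 and T4 in the immediate arm, and for that arm's share of the pooled pre-post result at T3. There PEP and interview mode change together, and the listed mixed-model terms do not separate them. Whether the deferred arm is affected depends on the unstated mode of T1.

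The size is conditional. Under assumed shifts of 0.1 to 0.3 SD, correlation 0.5 and no PEP effect, the 5% test at n = 36 rejects in about 9-42% of trials if all pre values are in person. The range is about 6-14% if T1 is by telephone and half the pairs are deferred. A shift in the opposite direction to PEP would mask a real effect instead. This should be corrected, but it does not invalidate the study.

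**What to change.** 1. Take all remaining T1 assessments by telephone, with the same standardized procedure as T3 and T4. In practice this means Woodhull (9 enrolled plus 11 planned), since all 71 Bellevue and Gouverneur participants have already been invited to PEP and T1 precedes the invitation.
2. Record the mode of every assessment, including those already done, and state the T1 mode in the report.
3. For statements about PEP at 3 months, where T1 was by telephone, use the concurrent randomised contrast: immediate T0-T3 change against deferred T0-T1 change. The Overview already times these to coincide, and a common mode shift cancels.
4. Label the immediate arm's T0-T3 and T0-T4 changes, and the pooled change at T3, as not separable from interview mode.
5. Report same-mode against cross-mode pairs, and T2 by mode, as sensitivity analyses only.

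**Cost.** One data field per assessment and a few analysis lines. With T1 by telephone, T1-T2 becomes cross-mode for deferred participants seen in person at T2; T0-T2 remains their same-mode comparison. T1 values already taken in person stay cross-mode against T3/T4 and are labelled so. The randomised contrast is also less precise than the paired test. At d = 0.48 it would need 69 per arm for 80% power, against 40 per arm enrolled before dropout (80/2), so it should be reported as an estimate with its confidence interval.
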